#### Missing data

By applying the above strategies of data collection (e.g., remuneration for providing data, sending reminders) and retention (e.g., general practices signing an agreement to participate), we expect to limit the risk of missing outcome data to a minimum. In case general practices leave the study, we will record the reason(s). To determine if it is relevant to deal with missing data by using multiple imputation (e.g., single value regression analysis), we will follow the recommendation by Jakobsen et al. [41] that the decision relies on being able to answer no to all of the following five key questions, i.e.;Is it valid to ignore missing data (rule of thumb: below 5% missing)?Too large proportions of missing data (rule of thumb: > 40%)?Is data only missing on the dependent variable?Is the missing completely at random assumption plausible?Is the missing not at random assumption plausible?

In case an answer is yes, we will use observed data only and then thoroughly discuss and report the extent of the missing data and the limitations.

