### Outcomes

#### Clinical outcomes

Table 2 shows the primary and secondary patient outcome measures. The primary patient outcomes are the percentage of patients with T2D and three types of co-morbidities on appropriate diabetes-related medication: ischemic heart disease and/or stroke; micro- or macro-albuminuria; and LDL > 2.5 mmol/L. To account for multiplicity, we use the Bonferroni correction method to adjust the *p*-values of the three primary clinical outcomes. The Bonferroni correction sets the significance cut-off at α/n [36], which means we only reject the null hypothesis of a primary clinical outcome if the *p*-value is less than 0.0167 (i.e., 0.05/3).

**Table 2 Tab2:** Overview of primary and secondary outcomes measures

Aspect	Outcome measure
Primary clinical outcome measures	Percentage of patients with T2D and ischemic heart disease and/or stroke being treated with glucagon-like peptide 1 receptor agonists (GLP1-RA) and sodium glucose cotransporter 2 (SGLT2) inhibitor
	Percentage of patients with T2D and micro/macro-albuminuria being treated with angiotensin-converting-enzyme-inhibitor (ACE) or angiotensin-2-receptorantagonist (AT2)
	Percentage of patients with T2D and LDL > 2.5 mmol/L being treated with statins
Secondary clinical outcome measures	Percentage of patients with T2D and HbA1c < 58 mmol/L
	Percentage of patients with T2D and HbA1c < 53 mmol/L
	Percentage of patients with T2D and blood pressure < 140 mmHg
	Percentage of patients with T2D and blood pressure < 130 mmHg
	Percentage of patients with T2D and low-density lipoprotein > 2.5 mmol/L
	Percentage of patients with T2D and microalbuminuria and LDL > 1.8 mmol/L
Primary competence and organization outcome measures	The extent to which the GP is confident managing T2D in general
	The extent to which the GP is skilled in making decisions on T2D in general
	The extent to which the GP is confident managing T2D and ischemic heart disease, stroke, peripheral artery disease, and heart failure
	The extent to which the GP is confident managing T2D and blood pressure
	The extent to which the GP is confident managing T2D and kidney disease
	The extent to which the GP is confident managing T2D and cholesterol
Secondary competence and organization outcome measures	GPs rating of the degree of relational coordination within the general practice
	GPs rating of the degree of relational coordination with the endocrinology department

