### Statistical analysis plan

Statistical significance is expressed in 95% two-sided confidence intervals. A *p*-value of < 0.05 will indicate statistical significance.

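### The missing-data rule's only example of multiple imputation is a single-value regression: a contradiction that would understate standard errors if followed literally, in a narrow branch of the plan

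*Protocol article*

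**What the plan says.** The Missing data section of the protocol article sets out when the trial will "deal with missing data by using multiple imputation (e.g., single value regression analysis". No other imputation technique is named. Whether to impute is settled by a screening list: "the decision relies on being able to answer no to all of the following five key questions". The first two questions bound the amount missing: "Is it valid to ignore missing data (rule of thumb: below 5% missing" and "Too large proportions of missing data (rule of thumb: > 40" (both in percent). The third asks "Is data only missing on the dependent variable". The last two ask whether data missing completely at random, and data missing not at random, are plausible. The fall-back is "In case an answer is yes, we will use observed data only", with the extent of missing data and the limitations reported and discussed.

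The section gives no expected proportion missing; it says only that the risk will be kept to a minimum.

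**The concern.** Multiple imputation creates several completed data sets by random draws, analyses each one, and adds the variation between them to the standard error. A regression that supplies a single value per gap does none of this. The later analysis counts predicted values as observations, so lost sample size and imputation error both drop out of the standard error.

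A kinder reading is that the phrase loosely describes a regression model for one incomplete variable, used inside multiple imputation. That fits the rule poorly too. Because of the third question, the branch is entered only when something besides the outcome is incomplete, so at least two variables need a model.

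The two readings give different p-values and intervals from the same data, and the text does not choose between them. At stake is the validity of inference for any outcome that reaches this branch.

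**Working it through.** **Step 1. The plan's own figures.** The document gives no missingness rate and no property of its imputation method that could be reproduced. Its one checkable error rate is the Bonferroni cut-off in the Clinical outcomes section: 0.05/3 = 0.0167, stated as "less than 0.0167 (i.e., 0.05/3". That is right. It covers only the three primary clinical outcomes. Other outcomes use 0.05, two-sided ("Statistical significance is expressed in 95% two-sided confidence intervals").

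**Step 2. Who reaches the imputation branch.** All five answers must be no: the missing share cannot be ignored (about 5% or more), is not above 40%, is not confined to the outcome, and neither missing completely at random nor missing not at random is plausible.

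- *Primary clinical outcomes.* A practice that sends no screenshot lacks only the outcome, so question 3 is yes and observed data are used. The Difference between intervention and control group section ties its control variables to survey outcomes. The Blinding section says control practices give no baseline data.
- *Survey outcomes.* The questionnaire also asks about the respondent and the practice, and covariates such as seniority and practice size are to be tested. A questionnaire that is not returned can remove outcome and respondent covariates together, so question 3 is no. The primary competence outcomes are in this group.

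**Step 3. Mechanism, in the simplest case.** Take n = 30 units, p = 3 coefficients (intercept, arm, one covariate) and m units with the outcome observed. Fill the rest with predictions from the same regression. The filled points have zero residual, so the coefficients and residual sum of squares stay as in the observed data, but the software uses n in place of m. Approximately:

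reported SE / correct SE = sqrt[ (m − p)/(n − p) × m/n ]

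The nominal 5% critical value on 27 df is 2.0518. The actual type I error is the two-sided tail of t on m − p df beyond 2.0518 × ratio. For 12 missing: sqrt(15/27 × 18/30) = sqrt(0.333) = 0.577; 2.0518 × 0.577 = 1.185; tail on 15 df = 25.5%.

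| Missing of 30 | m | SE ratio | 2.0518 × ratio | df | Type I error |
|---|---|---|---|---|---|
| 2 | 28 | 0.930 | 1.907 | 25 | 6.8% |
| 3 | 27 | 0.894 | 1.835 | 24 | 7.9% |
| 6 | 24 | 0.789 | 1.619 | 21 | 12% |
| 9 | 21 | 0.683 | 1.402 | 18 | 17.8% |
| 12 | 18 | 0.577 | 1.185 | 15 | 25.5% |

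This shows how the error arises. It is outcome-only missingness, which the plan sends to observed data, so it is not the case that counts.

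**Step 4. A case the rule does admit.** Simulation under no arm effect: 30 units, outcome and one covariate both missing, missingness depending on an observed practice variable, normal data, modest correlations, 5,000 trials per setting. All of these are assumptions. Type I error at nominal 5%:

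| Missing | Single fill |
|---|---|
| 2 of 30 | 7.2% |
| 10% | 7.8% |
| 20% | 11.9% |
| 30% | 17.3% |
| 40% | 26.5% |

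Observed data only gave 4.4-5.2% in these runs. A separate run of the same type of case gave about 7% to 25% for the single fill, about 3% to 5% for proper multiple imputation, and about 4% to 6% for observed data only. With 90 independent units the single fill still gave 6.9% to 24.5%, so more respondents do not cure it.

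**The case against.** The strongest reply is that the named method is multiple imputation and the phrase is only an example, inside a rule about whether to impute. The text never says that gaps are filled once or that fills are treated as observed. A regression model for one variable is an ordinary building block of multiple imputation. Arm and the stratification factors are known for every randomised practice, so such a model would not lack predictors. This stands: a reader might infer that the trial has committed itself to single imputation, and the wording does not support that.

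Second, it is tempting to say that missingness of 5% to 40% is enough to trigger imputation, and that a few filled-in practices could produce a false positive on a primary clinical outcome at 0.0167. That also fails. The percentage window is two conditions of five, and a missing screenshot is outcome-only missingness, which goes to observed data.

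Third, the number of data sets, pooling and degrees of freedom are details that an analysis plan commonly holds, and their absence here is no fault. Agreed. The point is that the one detail given conflicts with the method it illustrates.

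What the reply does not remove is the contradiction. Neither reading of the example yields a suitable procedure for the branch in which it would be used.

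**Conclusion.** The point holds as a contradiction in wording with a limited but real consequence. The literal reading leaves imputation uncertainty out of the standard error; the one-variable reading does not suit data missing on several variables.

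If the literal reading were followed in the imputation branch, type I error at nominal 5% would be about 7% near the low end of the window and about 25% at 40% missing. Under the assumed conditions both proper multiple imputation and the plan's own fall-back stay near nominal or below. These figures show direction and range; they are not a forecast. They rest on 30 units, normal data, modest correlations and data missing at random, and the documents give no expected missingness. Near 5% missing the inflation is modest.

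The reach is mainly survey outcomes with missing covariates, including the primary competence outcomes, and seldom the primary clinical outcomes. The wording should be corrected before the month-12 data are seen.

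**What to change.** Replace the parenthesis. State that, when the screening rule leads to imputation, the trial will use multiple imputation by chained equations, with several completed data sets created by random draws. The imputation model should contain arm, the stratification factors (number of full-time GPs and location) and the analysis covariates. Estimates should be pooled by Rubin's rules with small-sample degrees of freedom.

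For survey data, handle clustering of respondents within practice by a multilevel or practice-level term. Do not enter practice indicators alongside arm: arm is constant within a practice, so the two cannot be separated as ordinary predictors.

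The cost is a sentence or two of plan wording and a little code. The downside is wider intervals when data are missing.

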#### Clinical outcomes

Clinical outcomes will be collected from an IT-platform (DEN: “Diabetes Overblik”. ENG: “Diabetes Overview”) used by Danish general practices, which contains anonymous and aggregated diabetes data about patients (Additional file 3 shows screenshots). As per the agreement to participate in the study, each general practice assigns a contact person who will e-mail the screenshot of the data to the project group. Each general practice is renumerated for performing this activity. Data will also be obtained from nationwide Danish registries: The Clinical Laboratory Information System Research Database (LABKA), The Danish National Prescription Registry (DNPR), The Danish National Health Service Register (NHSR), The Danish Civil Registration System (CRS), and The Danish National Patient Register (NPR). Register data will be linked to the unique provider number of each general practice.

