#### Difference between intervention and control group

The main analysis concerns the difference between the intervention and control group at month 12. Data from the Diabetes Overview and general practice survey are analysed using simple, multiple, and logistic regression analyses. Analysis is done according to the intention-to-treat principle to test if the groups differ in terms of outcome measures. The analysis of survey data will take into account cluster effects using the intra-cluster correlation coefficient. Using *t*-test and *Χ*^2^ tests, depending on the outcome measure, it will be determined if randomization has resulted in systematically different groups. Survey data are tested to determine if questions or indices of questions are internally consistent (Cronbach alpha). In the regression analyses, control variables at the individual (e.g., seniority) and practice level (e.g., form and size of practice) are tested to determine its influence on survey outcomes.

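### When missing-not-at-random is plausible or over 40% is missing, the missing-data rule stops at observed data and states no analysis that bounds the bias

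*Protocol article*

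**What the plan says.** The Missing data section of the protocol article sets a definite rule. For imputation, "the decision relies on being able to answer no to all of the following five key questions". The questions ask whether missing data can be ignored (under 5%), whether too much is missing (over 40%), whether only the outcome is missing, whether missing-completely-at-random is plausible, and, last, "Is the missing not at random assumption plausible". After a yes to any of them, "In case an answer is yes, we will use observed data only", and the extent of missing data and the limitations are reported and discussed. No further analysis is attached to any branch.

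Four other places bear on this:

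- Difference between intervention and control group: "Analysis is done according to the intention-to-treat principle", with the Diabetes Overview and the survey named as the data analysed.
- Data collection, Clinical outcomes: a contact person in each practice e-mails a screenshot of the outcome data. National registers are a further source: "Register data will be linked to the unique provider number of each general practice". Neither this section nor Missing data gives the registers a role when a screenshot is absent.
- Blinding: practitioners know their arm.
- Intervention arm and Comparison arm: during the 12 months, intervention practices have a 90-minute webinar and four 45-minute conferences. Controls have usual support and receive the intervention afterwards.

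**The concern.** The five questions describe very different situations but lead to one response. Observed data are a reasonable answer when almost nothing is missing or when missingness is completely at random. They are not a sufficient answer when the team has just judged that missingness may depend on the unseen values, or that more than 40% is missing. A discussion of limitations tells the reader that bias is possible. It does not say how large the bias would have to be to change the conclusion.

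In this design the question may well arise. Practices know their arm, supply their own outcome data, and face different demands before month 12. Whether a practice reports could therefore depend on both arm and performance. With 15 practices per arm, a few silent practices are a sizeable fraction of one arm.

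**Working it through.** **The plan's own figures.** The Bonferroni cut-off reproduces: 0.05/3 = 0.0167. The three power values (0.8870, 0.9941, 0.9848) cannot be recomputed, because their inputs are in Additional file 5, which is not shown. They are not needed here.

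**Step 1: the five branches side by side.**

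| A yes means | Is observed data enough? |
|---|---|
| Under 5% missing | Yes, little can change |
| Over 40% missing | No, the result needs a range |
| Only the outcome missing | Yes, if missing at random given the model covariates |
| Missing completely at random plausible | Yes |
| Missing-not-at-random plausible | No, the bias is unknown in size and sign |

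**Step 2: check of the outcome-only branch.** A simulation used 4000 runs of 15 against 15 practices, with no true effect and only the outcome missing, at random given a measured covariate. Observed-data regression gave a mean estimate of -0.002 (SD 0.426). Multiple imputation from the same covariates gave -0.001 (SD 0.427). The two agree, so this branch is sound on its own terms.

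**Step 3: when the thresholds decide.** Counting practices (15 + 15 = 30, from the Abstract):

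- 1/30 = 3.3%, under the 5% rule
- 2/30 = 6.7%, above it
- 12/30 = 40.0%, not over 40%
- 13/30 = 43.3%, over 40%

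Between 2 and 12 lost practices, the last three questions decide.

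**Step 4: size of the bias.** With *m* of 15 practices missing in one arm and practices weighted equally, bias in that arm's mean = (*m*/15) × (observed mean − missing mean). The gaps are assumptions, since the article gives none.

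| Missing in one arm | Gap 10 points | Gap 20 points |
|---|---|---|
| 2 of 15 | 2/15 × 10 = 1.3 | 2/15 × 20 = 2.7 |
| 3 of 15 | 3/15 × 10 = 2.0 | 3/15 × 20 = 4.0 |

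The sign depends on which arm loses which practices. Losing weak intervention practices inflates the difference; losing weak control practices shrinks it.

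**Step 5: effect on the test.** This assumes a normal test of practice means, no true effect, and the gap *g* expressed in SDs of practice means. With 3 of 15 missing in one arm, shift = (3/15) × *g* and SE = √(1/15 + 1/12) = 0.387. The rejection probability is Φ(shift/SE − 2.394) + Φ(−shift/SE − 2.394), where 2.394 is the two-sided critical value at 0.0167. It equals 0.020, 0.032 and 0.053 for *g* = 0.5, 1 and 1.5, against a nominal 0.0167.

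**Step 6: what a bounding analysis would show.** If the observed practices in an arm average 50% (assumed), setting the missing ones to 0% or 100% gives:

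- 2 missing: 13/15 × 50 = 43.3% up to 43.3 + 2/15 × 100 = 56.7%
- 3 missing: 12/15 × 50 = 40% up to 40 + 3/15 × 100 = 60%

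**The case against.** The strongest defence is that declining imputation when missing-not-at-random is plausible is correct. Imputation under missing-at-random would not remove that bias. On this view the sentence only settles whether to impute, and sensitivity analyses belong in a fuller plan that an article need not repeat. The trial also works to limit missing data through signed consent before randomization, remuneration, up to three reminders, and the later offer of the intervention to controls. Registers are already listed as a source of clinical data.

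The first part stands, and for that reason more imputation is not the remedy. The rest does not dispose of the point. The article fixes an action for these branches and limits it to observed data followed by discussion. That is a stated rule and goes beyond an omitted detail. The retention measures make missing data less likely but do not say what happens when they fail.

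A reader might infer more than the documents support:

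- *That outcome-only missingness is handled wrongly.* It is not (Step 2).
- *That imputation can practically never be used.* The rule asks whether missing-not-at-random is plausible, which is narrower than whether it can be excluded. For the survey, a non-respondent may also lack respondent characteristics collected in the same questionnaire, so the outcome-only question is not automatically a yes.
- *That the rule contradicts intention-to-treat.* Nothing in the text excludes practices for withdrawal or non-adherence. An outcome nobody supplied is a missing-data problem, and the article treats it separately.

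**Conclusion.** The point holds for two of the five branches: missing-not-at-random plausible, and over 40% missing. There the only stated analysis is the one the team has reason to doubt, and nothing bounds the error.

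The consequence is conditional. It arises only if practices or respondents are missing, and a single lost practice falls under the 5% rule. The figures in Steps 4 and 5 rest on assumed gaps and on loss confined to one arm; the article gives no missing-data rates. A reader might conclude that the trial would overstate its effect, but the documents do not fix the direction. This is a worthwhile, inexpensive improvement to the rule. It does not show that the main result will be biased.

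**What to change.** Keep the five questions and add two rules to the Missing data section, fixed before month-12 data are seen.

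(a) If any practice sends no screenshot, repeat the analysis of the primary clinical outcomes from the linked registers for **all** randomized practices in both arms, using one definition throughout. Do not fill in non-senders alone: that would mix screenshot and register values, in proportions that could differ by arm. Limit this to outcomes the registers hold. The article does not say, for example, that any listed register contains blood pressure.

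(b) For survey outcomes, and for clinical outcomes not in the registers, keep observed data as the main analysis. Whenever the over-40% or the missing-not-at-random question is answered yes, also report best-worst and worst-best case analyses and delta-shift analyses by arm. Call the result robust only if the conclusion holds across them.

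The cost is a few sentences and some additional model runs; the registers are already a planned source. The downside is that a wide range may force a less firm conclusion.

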### Process evaluation

Applying a during-trial design nested in the RCT, we will collect process data at the onset, during and after the intervention. The process evaluation will be guided by the MRC framework for conduction and reporting process evaluations [42]. Quantitative process measures are collected by asking endocrinologists to register data in an excel-spreadsheet after each virtual conference. The quantitative process measures will capture two main topics (Table 4): *About the conference*, e.g., information on “number of doctors attended” and “number of patients discussed” and *The outcome of the conference*, e.g., “dialogue about medication changes” or “prevention of inappropriate medication.”

**Table 4 Tab4:** Process registration

The conference	Number conference (1–4)
	Number of participating general practitioners (number)
	Number of participating practice staff (number)
	Number of patients discussed (number)
Content of the conference	Discussed medical adjustments (yes/no)
	Discussed medical adjustments only according to guidelines (yes/no)
	Prevented inappropriate medication (yes/no)
	Discussed treatment targets (yes/no)
	Number of referred patients to the department of endocrinology? (number)
	Used the “Diabetes Overview”? (yes/no)

To enrich the quantitative analysis, a qualitative process evaluation will study the implementation and use of virtual specialist conferences between general practice and endocrinologists. The analysis will provide knowledge within the domains of intervention adherence, barriers and facilitators for implementing and using virtual specialist conferences, and organizational and contextual influences. The qualitative data are collected at month 12 and 24 using semi-structured interviews with GPs (*n* = 10), practice staff (*n* = 10), and endocrinologists (*n* = 4). The interview guide is based on implementation and change theory [43, 44]. To achieve maximum variation, respondents from general practice are purposefully selected from two types, that is, five GPs and five practice staff from the group of general practices that increased patient and general practice outcomes and five GPs and five practice staff from the group of general practices that achieved negative or unchanged outcomes. The research team performing the interviews and coding the qualitative analysis will not be delivering the intervention. Transcribed interview data is systematically coded using Nvivo (qualitative data processing programme). Coding is first done deductively based on implementation and change theory, and inductively to ensure that all themes in the data are identified. Data are then analysed using the display method to derive learning points and draw conclusions within and across informants and analytical categories [45]. The qualitative data analysis will take place prior to knowing trial outcomes.

